## Independence at home:

2a. Is the assistance of another person at home essential every day for some activities of daily living?

☐ Yes                      ☐ No (VS)    If no: go to 3

Note: for a NO answer they should be able to look after themselves at home for 24 hours if necessary, though they need not actually look after themselves. Independence includes the ability to plan for and carry out the following activities: getting washed, putting on clean clothes without prompting, preparing food for themselves, dealing with callers and handling minor domestic crises. The person should be able to carry out activities without needing prompting or reminding and should be capable of being left alone overnight.

2b. Do they need frequent help of someone to be around at home most of the time?

☐ Yes (lower SD)                      ☐ No (upper SD)

Note: for a NO answer they should be able to look after themselves at home up to eight hours during the day if necessary, though they need not actually look after themselves

2c. Was the patient independent at home before the injury?

☐ Yes                      ☐ No

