1155 -Incidence of morbidity/mortality (DIND; death due to vasospasm, DIND, infarcts or  
1156 complications due to anti-vasospasm therapy) by patient discharge.

1157 -Need of anti-vasospasm rescue therapy by patient discharge.

1158 -Clinical outcomes at week 12 and week 52, following assessment with modified Rankin  
1159 Scale (mRS) scored 0-6 (with incidence of 'Good' outcome scores 0-2) and Glasgow  
1160 Outcome Scale (extended) (GOSE) scored 0-8 (with incidence of 'Favourable' outcome  
1161 scores 6-8), together with the Montreal Cognitive Assessment Tool (MOCA) (score 0-30  
1162 higher better) and Health related quality of life, assessed using the EQ-5D-5L and SF36. The  
1163 Length of stay in hospital and the ICU will also be assessed as measures of clinical outcome .  
1164

1165 The additional information reported as an addendum to the final report will specifically  
1166 include the final assessment for clinical outcome (mRS and GOSE), assessed at week 52,  
1167 together with any additional adverse events (specifically those that are CNS related), together  
1168 with the MOCA, EQ-5D-5L and SF36.

1169 These data can be considered binary, ordered categorical or interval in nature.

1170 All binary outcomes will be evaluated using the same methods as those for the primary  
1171 endpoint (Fishers exact test).

1172 Ordered categorical data will be analysed using the Cochran-Mantel-Haenzel (CMH) test  
1173 (with modified ridits). Ordinal logistic regression may be supplemented if other covariates of  
1174 interest are identified (e.g. age, gender, WFNS).

1175 Normally distributed Interval data will be analysed using an analysis of variance (ANOVA)  
1176 model including treatment group as fixed effect and (if possible) baseline or other  
1177 explanatory variables as covariates (e.g. age, gender, WFNS). Estimates of treatment effects  
1178 and treatment differences will use LS means and 95% confidence intervals.

1179 Non-parametric alternatives, however, will be substituted if these data are non-normally  
1180 distributed (eg: Length of stay). This may take the form of the Wilcoxon rank sum test or a  
1181 ranked based ANOVA model.

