| 
The Glasgow Outcome Scale (GOS) is a global scale for functional outcome that rates patient status into one of five categories: Dead, Vegetative State, Severe Disability, Moderate Disability or Good Recovery. The Extended GOS (GOSE) provides more detailed categorization into eight categories by subdividing the categories of severe disability, moderate disability and good recovery into a lower and upper category:
 
Table 1: Extended Glasgow Outcome Scale (GOSE)
 

1	Death	D	

2	Vegetative state	VS	

3	Lower severe disability	SD -	

4	Upper severe disability	SD +	

5	Lower moderate disability	MD -	

6	Upper moderate disability	MD +	

7	Lower good recovery	GR -	

8	Upper good recovery	GR +	

 |                           |      | 1 | Death | D | 2 | Vegetative state | VS | 3 | Lower severe disability | SD - | 4 | Upper severe disability | SD + | 5 | Lower moderate disability | MD - | 6 | Upper moderate disability | MD + | 7 | Lower good recovery | GR - | 8 | Upper good recovery | GR + |

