## Conciousness:

1. Is the head-injured person able to obey simple commands or say any words?

☐ Yes                      ☐ No (VS)

Note: anyone who shows the ability to obey even simple commands or utter any word or communicate specifically in any other way is no longer considered to be in vegetative state. Eye movements are not reliable evidence of meaningful responsiveness. Corroborate with nursing staff and/or other caretakers. Confirmation of VS requires full assessment.

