**Return to normal life:**

8a. Are there any other current problems relating to the injury which affect daily life?

☐ Yes (Lower GR)

☐ No (Upper GR)

Note: other typical problems reported after head injury: headaches, dizziness, sensitivity to noise or light, slowness, memory failures and concentration problems.

8b. If similar problems were present before the injury, have these become markedly worse?

☐ Yes

☐ No

9. What is the most important factor in outcome?

☐ a. Effects of head injury

☐ b. Effects of illness or injury to another part of the body

☐ c. A mixture of these

Note: extended GOS grades are shown beside responses on the CRF. The overall rating is based on the lowest outcome category indicated.

Areas in which there has been no change with respect to the pre-trauma situation are ignored when the overall rating is made

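### The appended GOSE interview prints the vegetative-state grade beside the answer that means independent at home, which could misrate patients; the stated GOSE ranges starting at 0 also do not match the 1-8 scale.

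*Protocol*

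**What the plan says.** GOSE is an exploratory endpoint at weeks 12 and 52, with 6-8 counted as favourable (Protocol, Exploratory Outcome Endpoints). The instrument is reproduced in Appendix 3.

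- **Item 2a, independence at home.** The 'No' answer reads "No (VS) If no: go to 3". The note beneath it says "for a NO answer they should be able to look after themselves at home for 24 hours if necessary".
- **Closing note of the interview.** It states that "extended GOS grades are shown beside responses on the CRF" and that "The overall rating is based on the lowest outcome category indicated". It then adds an exception: "Areas in which there has been no change with respect to the pre-trauma situation are ignored when the overall rating is made".
- **Item 1, consciousness.** 'No' is also labelled (VS). The note says that a person who obeys commands, speaks or can "communicate specifically in any other way is no longer considered to be in vegetative state".
- **Scale.** Appendix 3 says that the extended version "provides more detailed categorization into eight categories", and its Table 1 numbers them 1 (death) to 8 (upper good recovery).
- **Ranges in the body of the protocol.** The Efficacy Endpoints text of the statistical section has "Outcome Scale (extended) (GOSE) scored 0-8 (with incidence of 'Favourable' outcome" scores of 6-8. The Exploratory Outcome Endpoints section gives the unfavourable range as 0-5, once for week 12 and once for week 52.

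**The concern.** The (VS) label is correct on 'No' at item 1, where it means that the person neither obeys commands nor speaks. At item 2a, 'No' means the opposite of severe impairment. The line even sends the interviewer on to shopping, travel, work and leisure, a path that makes no sense for a vegetative patient.

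The label is not decoration. The closing note makes the printed grades the input to the score and takes the minimum. One wrong low label therefore overrides every other answer.

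What is at stake is the favourable-outcome proportion at both follow-up visits and the ordering of the scale. The protocol gives the 6-8 cut some weight: its Population section cites that outcome from an earlier trial of nimodipine microparticles when excluding WFNS grades I and II.

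**Working it through.** **1. Codes.** From Table 1 of Appendix 3: death 1, VS 2, lower SD 3, upper SD 4, lower MD 5, upper MD 6, lower GR 7, upper GR 8.

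**2. Rule.** Rating = minimum of the codes printed beside the answers given.

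**3. Grades open to a patient who answers 'No' at 2a.** The skip to item 3 bypasses 2b, the only place where lower SD (3) is assigned. The remaining labels are upper SD (items 3a, 4a), lower and upper MD (items 5b, 6b, 7b), lower GR (items 6b, 7b, 8a) and upper GR (item 8a). Without the (VS) label, the possible ratings are therefore 4 to 8.

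**4. Example paths, all with 2a = 'No'.**

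| Other answers | Label removed | (VS) counted | Home area dropped under the no-change exception |
|---|---|---|---|
| No restriction anywhere | 8 | min(2, 8) = 2 | 8 |
| 8a 'Yes' only | 7 | min(2, 7) = 2 | 7 |
| 5b, reduced work capacity | 6 | min(2, 6, 8) = 2 | 6 |
| 5b, sheltered work or unable to work | 5 | min(2, 5, 8) = 2 | 5 |
| 3a 'No' | 4 | min(2, 4, 8) = 2 | 4 |

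For comparison, a patient who needs daily help (2a 'Yes') is rated 3 if 2b is 'Yes' and 4 if 2b is 'No', taking the best answers elsewhere. With the label counted, a fully recovered patient (2) ranks below a dependent one (3 or 4), so the order is inverted.

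**5. Does the no-change exception rescue the rating?** For a patient independent both before and after the haemorrhage, dropping the home area restores 4-8, as the last column shows. Applying it needs the pre-injury status at home, which is item 2c. The same 'No' answer skips 2c, so the form does not record what the exception needs for exactly these patients.

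**6. Weight per patient.** With 20 patients per arm, one patient with a true score of 6-8 recorded as 2 moves that arm's favourable proportion by 1/20 = 5 percentage points; k such patients move it by 5k points. The documents give no basis for choosing k. A patient whose true score is 4 or 5 is unfavourable either way and does not move it.

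**7. Range.** The original scale has five categories, three of which are split in two: 2 + 3 × 2 = 8 categories, numbered 1-8. The stated 0-8 has nine codes, so it does not reproduce. Likewise, 0-5 plus 6-8 is 6 + 3 = 9 codes against eight categories; the matching unfavourable range is 1-5. No text defines a category 0. A death coded 0 or 1 is below 6 in both cases, so the favourable split does not change.

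**The case against.** The strongest reply is that no competent assessor would record an independent patient as vegetative. The item 1 note rules out that grade for anyone who communicates and asks for full assessment before it is confirmed. The item 2a line itself sends the interviewer on to questions about shopping and travel. Outcomes are collected by trained, blinded personnel, and the no-change exception can discard the home area. GOSE is exploratory, and mRS is measured at the same visits with its own scale.

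Much of this stands. A reader might infer that every independent patient will be scored 2 and that the favourable proportion will be 0% in both arms. The documents do not support that: it requires the label to be applied mechanically against the item 1 note, and neither the CRF nor any grade derivation is available to show that it is. Nor is a bias between arms shown, since both arms use the same form and the assessors are blinded.

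A reader might also infer that deaths will be split between codes 0 and 1 and so distort the Cochran-Mantel-Haenszel test. That is speculation too. The only anchored scale gives death = 1, and the protocol does not say that deaths would be coded in two ways.

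What does not stand is the idea that the form corrects itself. The item 1 note contradicts the 2a label, but nothing says which prevails, and the exception lacks its input because 2c is skipped. A programmed minimum of printed grades would meet neither safeguard.

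**Conclusion.** The point holds as an internal contradiction in a trial instrument, with a possible scoring consequence. Item 2a 'No' carries a grade that its own note and the item 1 note exclude, and the lowest-grade rule turns that label into a potential rating of 2 for patients who would otherwise be rated 4-8.

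Its size depends on how literally the form is applied: nil if assessors overlook the label, 5 percentage points per affected patient with a true score of 6-8 in an arm of 20, and an inverted scale if the printed grades are programmed as they stand. This assumes that the CRF repeats the appendix labels, which cannot be checked from the protocol.

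The 0-8 and 0-5 ranges are plainly inconsistent with the appended scale but have no effect on the 6-8 split by themselves. The primary endpoint (angiographic vasospasm) and the sample size are untouched. This is a small correction worth making, not a flaw in the design.

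**What to change.** - **Item 2a.** Confirm the label on the typeset page, then delete (VS) from the 'No' answer in Appendix 3. Make the same deletion in the CRF and in any programmed grade derivation, if it is reproduced there. Keep it on item 1.
- **Ranges.** Change 0-8 to 1-8 in the Efficacy Endpoints text of the statistical section, and both instances of 0-5 to 1-5 in the Exploratory Outcome Endpoints section (weeks 12 and 52). State that death is coded 1.
- **Check.** Compare the CRF grade derivation with the corrected form before week 12 ratings are made. If ratings already exist, re-derive them from the item answers where these were kept.

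The cost is one label and three ranges in the protocol, plus a check of the CRF. Nothing changes for patients, visits, sample size or the primary analysis.

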## Independence outside home:

3a. Are they able to shop without assistance?

☐ Yes                      ☐ No (upper SD)

Note: this includes being able to plan what to buy, take care of money themselves and behave appropriately in public. They need not normally shop, but must be able to do so.

3b. Were they able to shop without assistance before?

☐ Yes                      ☐ No

4a. Are they able to travel locally without assistance?

☐ Yes                      ☐ No (upper SD)

Note: they may drive or use public transport to get around. Ability to use a taxi is sufficient, provided the person can phone for it themselves and instruct the driver.

4b. Were they able to travel locally without assistance before the injury?

☐ Yes                      ☐ No

## Work:

5a. Are they currently able to work (or look after others at home) to their previous capacity?

☐ Yes    If yes, go to 6    ☐ No

5b. How restricted are they?

- a. Reduced work capacity? ☐ a. (Upper MD)
- b. Able to work only in a sheltered workshop or non-competitive job or currently unable to work? ☐ b. (Lower MD)

5c. Does the level of restriction represent a change in respect to the pre-trauma situation?

☐ Yes

☐ No

**Social and Leisure activities:**

6a. Are they able to resume regular social and leisure activities outside home?

☐ Yes

If yes, go to 7

☐ No

Note: they need not have resumed all their previous leisure activities, but should not be prevented by physical or mental impairment. If they have stopped the majority of activities because of loss of interest or motivation, then this is also considered a disability.

6b. What is the extent of restriction on their social and leisure activities?

a. Participate a bit less: at least half as often as before injury

☐ a. (Lower GR)

b. Participate much less: less than half as often

☐ b. (Upper MD)

c. Unable to participate: rarely, if ever, take part

☐ c. (Lower MD)

6c. Does the extent of restriction in regular social and leisure activities outside home represent a change in respect or pre-trauma

☐ Yes

☐ No

**Family and friendships:**

7a. Has there been family or friendship disruption due to psychological problems?

☐ Yes

☐ No

If no, go to 8

Note: typical post-traumatic personality changes are: quick temper, irritability, anxiety, insensitivity to others, mood swings, depression and unreasonable or childish behaviour.

7b. What has been the extent of disruption or strain?

a. Occasional - less than weekly

☐ a. (Lower GR)

b. Frequent - once a week or more, but not tolerable

☐ b. (Upper MD)

c. Constant - daily and intolerable

☐ c. (Lower MD)

7c. Does the level of disruption or strain represent a change in respect to pre-trauma situation?

☐ Yes

☐ No

Note: if there were some problems before injury, but these have become markedly worse since the injury then answer yes to question

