### 275 **Exploratory Outcome Endpoints**

276 The exploratory outcome endpoints are:

- 277 • Incidence of vasospasm-related morbidity/mortality within 21 days or before  
278 patient discharge, defined by at least one of the following:
  - 279 a. DIND.
  - 280 b. Death caused by vasospasm, delayed ischemic neurological deficit (DIND),  
281 infarcts or complications due to anti-vasospasm therapy.
  - 282 c. The need for anti-vasospasm rescue therapy.
- 283 • Length of Intensive Care Unit (ICU) stay
- 284 • Length of Hospital Stay
- 285 • Clinical outcome at Week 12 post-aneurysm rupture as measured by:
  - 286 a. Modified Rankin Scale (mRS) – “Good Outcome” defined as mRS of 0 to 2
  - 287 b. Glasgow Outcome Scale (Extended) (GOSE) – “favourable outcome” of 6-8,  
288 “unfavourable outcome” of 0-5
  - 289 c. Montreal Cognitive Assessment tool (MoCA) - score 0-30 higher better
  - 290 d. Health related quality of life assessed using the EQ-5D-5L and SF36.

- Long-term Clinical outcome at Week 52 post-aneurysm rupture as measured by:
  - a. Modified Rankin Scale (mRS) – “Good Outcome” defined as mRS of 0 to 2
  - b. Glasgow Outcome Scale (Extended) (GOSE) – “favourable outcome” of 6-8, “unfavourable outcome” of 0-5
  - c. Montreal Cognitive Assessment tool (MoCA) - score 0-30 higher better
  - d. Health related quality of life assessed using the EQ-5D-5L and SF36.

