1332 The CRF is defined as source data for rating scales i.e. Glasgow Coma Scale.

1333

1334 **STUDY MONITORING**

1335 It is understood that the study monitor(s) will contact and visit the investigator/clinical site  
1336 before the study, regularly throughout the study and after the study has been completed. At  
1337 these visits, the monitor(s) will inspect various study records; case report forms, investigator  
1338 site file and source data (patient records). No information in these records about the identity  
1339 of the subjects will leave the Trial site. The sponsor will maintain confidentiality of all  
1340 subject records. The investigator and / or site staff will be expected to be available if  
1341 requested by the monitor.

1342

1343 **QUALITY ASSURANCE**

1344 The sponsor (Brain Implant Therapeutics Pharma GmbH) or representative may perform an  
1345 audit at any time according to the sponsor's Standard Operating Procedure (SOP), in order to  
1346 verify whether the study is being conducted according to GCP.

1347

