| 5                                                                                                                                                                                                                                                                                                                                                                                                                                                                                                                                                                                                                                                                                                                                                                                                                                                                                                                                                                                                          | Lower moderate disability | MD - |   |       |   |   |                  |    |   |                         |      |   |                         |      |   |                           |      |   |                           |      |   |                     |      |   |                     |      |

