| 6                                                                                                                                                                                                                                                                                                                                                                                                                                                                                                                                                                                                                                                                                                                                                                                                                                                                                                                                                                                                          | Upper moderate disability | MD + |   |       |   |   |                  |    |   |                         |      |   |                         |      |   |                           |      |   |                           |      |   |                     |      |   |                     |      |

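### GOSE interview item 7b: option b repeats option c's tolerability condition, so frequent but tolerable strain has no box and its grade is left to the rater (minor)

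*Protocol*

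**What the plan says.** Appendix 3 of the protocol reproduces the GOSE post-discharge interview. Under Family and friendships, item 7b asks how far relationships have been strained and prints a grade beside each answer:

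- Option a, "a. Occasional - less than weekly": Lower GR, grade 7.
- Option b, "b. Frequent - once a week or more, but not tolerable": Upper MD, grade 6 ("Upper moderate disability" in Table 1 of the appendix).
- Option c, "c. Constant - daily and intolerable": Lower MD, grade 5 ("Lower moderate disability" in the same table).

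The note that closes the interview gives the scoring rule: "The overall rating is based on the lowest outcome category indicated". It adds that areas unchanged from before the event do not count.

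The Exploratory Outcome Endpoints section lists "Glasgow Outcome Scale (Extended) (GOSE) – “favourable outcome” of 6-8" at weeks 12 and 52, with lower grades unfavourable. Under Efficacy Endpoints in the statistical section, binary outcomes go to Fisher's exact test and ordered categories to the CMH test with modified ridits.

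**The concern.** The three answers are meant to form a ladder of increasing severity, and each rung sets a grade. Options b and c carry the same tolerability condition in different words. The contrasting conjunction in b leads the reader to expect the opposite condition from the one printed. The neighbouring ladder in item 6b, on social and leisure activities, steps down in order without this overlap.

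Two things follow. Patients whose strain is frequent but bearable cannot be placed by the form, so the rater must choose a box against its wording or leave the item blank. Patients whose strain is daily and unbearable satisfy two boxes, and those boxes lie either side of the favourable cut. At stake is the consistency of the GOSE grade between raters, which the structured interview is there to provide. A statistical analysis plan cannot repair this, because the defect acts when the box is ticked.

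**Working it through.** The protocol states no figure on this point, so there is none to reproduce. The check lists every situation that item 7b can meet and reads the printed options against it.

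**Inputs.** Three frequencies (under weekly; weekly or more but not daily; daily) crossed with two tolerability states give 3 × 2 = 6 situations. Option a sets a frequency condition only. Options b and c each set a frequency and a tolerability condition. Grades come from Table 1 of Appendix 3 and the favourable cut (6 to 8) from the Exploratory Outcome Endpoints.

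| Frequency | Tolerability | Options met as printed | Options met if b were the tolerable step |
|---|---|---|---|
| Under weekly | tolerable | a (7) | a (7) |
| Under weekly | intolerable | a (7) | a (7) |
| Weekly or more, not daily | tolerable | none | b (6) |
| Weekly or more, not daily | intolerable | b (6) | none |
| Daily | tolerable | none | b (6) |
| Daily | intolerable | b (6) and c (5) | c (5) |

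**Count.** As printed, 3 situations have exactly one option, 2 have none and 1 has two (3 + 2 + 1 = 6). With b as the tolerable step, 5 have exactly one option, 1 has none and none has two.

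**Situations with no option.** The likely ways out are to tick a (7), to tick b against its wording (6), or to leave 7b blank and let the other domains decide, in which case the grade can be as high as 7 or 8. Grades 6, 7 and 8 are all favourable, so these choices move the ordinal score but not the binary outcome. Sending daily tolerable strain to c would give 5, but the rater would have to follow c's frequency word and disregard its tolerability condition. The point does not rest on that.

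**Situation with two options.** If b and c are both ticked, the lowest-grade rule gives min(6, 5) = 5, unfavourable. If only c is ticked, the grade is again 5. If only b is ticked, which its wording permits, the grade is 6, favourable. Only this last case moves a patient across the cut.

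**When item 7 matters at all.** For the 5-versus-6 distinction, no other domain may already give 5 or lower, and the strain must be a change from before the event; otherwise the closing note removes it from the rating.

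**The case against.** The case for leaving this alone has four parts.

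1. The form resolves the overlap. The lowest-grade rule settles a double tick, and only option c names constant, daily strain, so a rater reading the headings would go to c. This largely stands. It does not cover a rater who ticks b alone, and it does nothing for the two situations with no box.

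2. The gap does not reach the favourable cut. This stands for the outcomes set out above (6, 7 or 8), so the harm from the gap is noise in the ordinal analysis.

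3. The size is unknown. This stands. A reader might infer that the misprint could overturn a result: in an arm of 20, one patient is 1/20 = 5 percentage points, and 11/20 versus 4/20 favourable gives a Fisher p of 0.048 while 10/20 versus 4/20 gives 0.096. Those counts are chosen to sit at the threshold. The protocol does not say how often item 7 decides the grade; an assumed 5% to 15% (1 to 3 of 20) has no basis in it, and only some of those patients would be mis-graded. Raters at weeks 12 and 52 are to be blinded and the wording is the same in both arms, so no direction of bias follows.

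4. The instrument is a third party's, and the correct wording cannot be confirmed from the protocol. This also stands and shapes the fix. It does not rescue the printed line, whose inconsistency is visible without the source.

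A reader might also infer that the true answer is lost once the form is completed, because the section on direct access to source data says "The CRF is defined as source data for rating scales i.e. Glasgow Coma Scale". That sentence names a different scale, and the interview note says grades are printed beside the responses on the CRF, so the item-level answer should be there. The protocol does not support a claim that answers are irrecoverable.

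**Conclusion.** Option b of item 7b is wrong as printed. Tolerable strain occurring weekly or more often has no option, and its grade depends on the rater. Daily intolerable strain satisfies two options, but the favourable/unfavourable split is affected only if b alone is ticked.

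The severity is minor. GOSE is exploratory; the primary and secondary endpoints and the sample size are untouched. The misprint applies to both arms, so the expected effect is added noise. Its size cannot be computed from the protocol, and no claim that it would change a test result is supported.

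The conclusion assumes that the interview is applied as printed. The CRF is not shown, so whether it carries the same wording is unknown. That b should be the tolerable step is an inference from the order of the options and the contrast in the sentence.

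**What to change.** - Check item 7b against the published structured interview cited in Appendix 3. Then correct option b there, and on the CRF if it carries the same wording, so that b and c are mutually exclusive and ordered. The form's own logic points to weekly or more often but tolerable for b, with c unchanged.
- Add one line of rater instruction for strain that is weekly or more but not daily, and intolerable. The printed b covers that situation; the corrected b would not.
- Query any item 7b answers already collected, with the blinded rater confirming the answer before database lock.

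The cost is one corrected line, one rater note and possibly a few data queries. No extra visits or patients are needed.
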